Participants are assessed at multiple time points (T0: prior to the program, T1: mid-program, T2: end of the program, T3: post-program follow-up). These longitudinal evaluations, based on standardized tools, will enable a detailed analysis of participants’ well-being progression and the specific effects attributable to the group intervention. This study is part of an action-research framework, integrating clinical intervention with the production of scientific knowledge while offering transferable recommendations for other support programs aimed at vulnerable young adults.

**Table 1 Tab1:** Summary table of the research methodology

	Study 1	Study 2	Study 3
Type of study	Quantitative	Qualitative	Longitudinale
Method	Cohort study using self-administered questionnaires	Semi-structured interviews Rorschach test Adult Attachment interview (AAI)	Group intervention Self-administrated questionnaires
Eligibility criteria	Participant aged > 18 Resident in a Housing center Fluent in French adult participants who are not under guardianship (tutelle) or curatorship (curatelle).	Participant aged > 18 Fluent in French Any substance user Migratory background	Same as study 1
Exclusion criteria	Minors Do not speak and read French Under Guardianship or Curatorship	Minors Do not speak and read French Under Guardianship or Curatorship	Minors Do not speak and read French Under Guardianship or Curatorship
Main Outcomes	Substance use prevalence Mental health representations Mental health aspects (anxiety, depression) Childhood trauma	Substance use, trauma and migration trajectory (semi-structure interview) Attachment style (AAI tool) Psychological functioning (Rorschach test)	Substance use Perception of mental health care Wellness
Analysis	Quantitative analysis	Thematic analysis	Quantitative and qualitative analysis

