The longitudinal study will follow the same inclusion criteria as the qualitative study (Study 2). However, participation in the group sessions is open to all volunteers for each session, regardless of whether they are substance users. Informed consent will be systematically obtained before each session, ensuring fully informed participation. Promotion of the groups will be conducted through widespread dissemination of informational posters, email communications via the management of the partner structures, and during informational meetings. A follow-up meeting will be organized 15 days later to conduct the initial T0 evaluation with the volunteers.

The “Well-Being coffee group” intervention is implemented in several formats (see Fig. 1). Some groups will take place in person, others via videoconference, all conducted by the same psychologist throughout the sessions. Additionally, a control group will consist of participants who underwent the initial evaluation (T0) but did not attend any sessions. The inclusion of this control group allows for the assessment of changes in psychological and behavioral outcomes over time, comparing those who received the intervention to those who did not. The choice of this comparator was made based on feasibility and ethical considerations, ensuring that participants were not deprived of potential care while maintaining an adequate framework for evaluating the intervention’s effects. Across all formats, participation is voluntary, following a prior information phase and the signing of an informed consent form. Participants will complete standardized evaluation questionnaires at multiple time points (T0, T1, T2, T3).

The discussion groups aim to provide a supportive and open space for free expression. Their objective is to allow participants to articulate their thoughts, emotions, and personal experiences, as well as those evoked by group discussions on various themes, including identity, substance use, migratory experiences, and mental health. The impact of the intervention will be assessed regularly using standardized tools to measure levels of anxiety, depression, and changes in attitudes and willingness to seek help. Finally, a global satisfaction scale will be used at the end of the sessions to collect participants’ subjective feedback on their experiences within the groups (see Fig. 1).

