### Data analysis

#### Study 1

The research team will conduct statistical analyses using R. The cross-sectional study will characterize the study population through descriptive and multivariate analyses (e.g., Chi-square/Fisher’s exact tests, correlation tests, ANOVA, etc.). We will adhere to the STROBE guidelines for epidemiological studies [58]. A significance level of 0.05 will be applied for statistical analysis.

#### Study 2

A thematic analysis of the data from the semi-structured interviews will be conducted using NVivo 15 software. Moreover, the findings from the Rorschach test will be analyzed using a methodology for interpreting projective material [48], with the aim of highlighting underlying psychic processes, particularly those related to attachment dynamics early traumas, the defensive mechanisms of participants. Additionally, the interviews reported from the AAI assessment will be coded by MN and AF under the supervision of a certified reliable coder [name] using the Adult Attachment Scoring and Classification System [49].

#### Study 3

For the group intervention, a Bonferroni correction will be applied to all *p*-values in t-tests. Cronbach’s alpha will be used to assess the reliability of the scales. Various analyses will be conducted to evaluate pre- and post-intervention effects as well as dose-response effects, including Student’s t-tests, repeated-measures ANOVA, and linear regression.

Primary and secondary outcomes will be analyzed using linear mixed models, incorporating a random group effect if estimation permits. The primary outcome measure is the variation in the total score on the ATSPPH-S at 9 months, calculated using dimensional scoring algorithms. Changes in the primary outcome and the relative effectiveness of the four intervention modalities will be assessed using mixed regression models, utilizing all available data while accounting for participant, time, and group levels. The underlying distribution for the mixed regression model will be determined based on residual distribution.

Per-protocol analyses will also be performed to test robustness. ANCOVA analyses may be conducted as needed to control for confounding variables that could influence the results. If data distribution is non-parametric, analyses such as Mann-Whitney, Wilcoxon, and Kruskal-Wallis tests will be employed.

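### Study 3 compares attenders with volunteers who never came, yet attributes the difference to the intervention and leaves confounder adjustment discretionary

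*Protocol article*

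**What the plan says.** All references are to the protocol article.

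- **Who enters.** Under Procedures, Study 3, after the groups have been publicised, "A follow-up meeting will be organized 15 days later to conduct the initial T0 evaluation with the volunteers".
- **Who attends.** The same section says that "participation in the group sessions is open to all volunteers for each session, regardless of whether they are substance users", and that "Across all formats, participation is voluntary, following a prior information phase and the signing of an informed consent form". The text describes no random or rule-based allocation to attendance or non-attendance.
- **Who is a control.** "a control group will consist of participants who underwent the initial evaluation (T0) but did not attend any sessions". The stated purpose is to assess change over time by "comparing those who received the intervention to those who did not".
- **Why this comparator.** "The choice of this comparator was made based on feasibility and ethical considerations". The article regards the resulting framework as adequate.
- **What is claimed.** Under Methods/design, the repeated assessments are meant to permit analysis of "the specific effects attributable to the group intervention".
- **How it is analysed.** Under Data analysis, Study 3, the primary outcome is the change in ATSPPH-S total score at 9 months. It is modelled by mixed regression with participant, time and group levels. On confounding, the only provision is that "ANCOVA analyses may be conducted as needed to control for confounding variables that could influence the results".

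**The concern.** Control status is something a volunteer does after T0. Methods/design describes six monthly sessions, so membership of the control group is final only when the last session has passed.

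The outcome makes this more serious. ATSPPH-S measures attitude toward seeking psychological help, and that attitude could well decide whether a volunteer comes to a group led by a psychologist. The Background itself describes reluctance toward psychological care among these residents. Attenders and never-attenders may therefore differ at T0 on the primary scale, and may differ in how they would have changed without any sessions.

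If the plan is followed as written, a self-selected contrast can be reported as the effect of the intervention. Whether and how to adjust can also be decided after the results are known.

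**Working it through.** **1. The planning figure.** Participants, Study 3, gives d = 0.7, alpha = 0.05 and 55 per group, 165 in total. Power is not stated. A two-sample t-test with two-sided alpha 0.05 needs 34, 44 or 55 per group for 80%, 90% or 95% power, so 55 reproduces at 95% (exact power 95.3%), and 3 × 55 = 165. The calculation takes the groups as comparable apart from the intervention. The point here does not depend on this arithmetic.

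**2. What a change score does under a common mean.** Let D be the T0 gap (attenders minus never-attenders, in SD) and r the correlation between T0 and 9 months. Neither is in the documents, so both are assumed. With no intervention effect, equal variances and regression of both groups to one common mean, the expected 9-month gap is rD. The change contrast is then rD - D = -(1 - r)D.

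| D | r = 0.5 | r = 0.6 | r = 0.7 |
|---|---|---|---|
| 0.3 | -0.15 | -0.12 | -0.09 |
| 0.5 | -0.25 | -0.20 | -0.15 |

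A mixed model that leaves the T0 means free in each group and tests group by time estimates this same kind of change contrast.

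**3. The opposite assumption.** If the two groups differ stably and would have moved in parallel, the 9-month gap stays at D and the change contrast is unbiased. Adjusting for T0 with within-group slope r then leaves D - rD = (1 - r)D, which is +0.09 to +0.25 SD for the same inputs. Neither analysis is right by default.

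**4. Selection through an unmeasured motive.** A simulation with no true effect (400,000 volunteers per setting) used these assumptions: a coefficient of 0.6 for T0 on the outcome; an unmeasured readiness correlated 0.5 with the T0 score; and readiness driving attendance (log-odds a per SD) and also the outcome (coefficient b). Results are in T0 SD.

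| a | b | T0 gap | Change contrast | Adjusted for T0 | Adjusted for T0 and readiness |
|---|---|---|---|---|---|
| 0.5 | 0 | 0.236 | -0.095 | 0.000 | 0.000 |
| 0.5 | 0.2 | 0.236 | 0.002 | 0.074 | 0.001 |
| 0.5 | 0.4 | 0.233 | 0.098 | 0.146 | 0.003 |
| 1.0 | 0 | 0.415 | -0.163 | 0.004 | 0.004 |
| 1.0 | 0.2 | 0.416 | 0.001 | 0.131 | -0.001 |
| 1.0 | 0.4 | 0.413 | 0.165 | 0.259 | 0.000 |

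The change contrast runs from -0.16 to +0.17 SD and the T0-adjusted contrast from 0.00 to 0.26 SD. Only adjustment for readiness as well brings the bias to about zero in every setting.

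**5. What a residual difference does to the test.** Take 55 v 55 (assuming that the control is one of the groups of 55), no true effect and a two-sided 0.05 test. A residual selection difference on the analysed outcome gives these false-positive rates:

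| Residual difference (SD) | 0.1 | 0.2 | 0.3 | 0.4 | 0.5 |
|---|---|---|---|---|---|
| False-positive rate | 8.1% | 18.0% | 34.5% | 54.7% | 73.8% |

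A larger sample does not remove the bias.

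**The case against.** The comparator is disclosed and justified on feasibility and ethical grounds, and the study is presented as action research. T0 is not ignored: it enters the change score and is one of the repeated measurements. Mixed models, per-protocol checks and ANCOVA are all named. Covariate lists, weighting and balance tables are usual content for an analysis plan that is not shown here.

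Much of this is fair. Feasibility and ethics can explain the absence of randomisation, and a missing covariate list is not the complaint. What remains is what the article itself fixes: a control group defined by non-attendance, confounder control that is merely permitted, and wording that attributes effects to the intervention. The per-protocol analysis does not help, since the main contrast already follows attendance.

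A reader might infer more than the documents support:

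- *That every arm is self-selected.* The text shows this for the control group only. How participants come to in-person or videoconference groups is not stated in the text, and the flowchart is not available in the copy reviewed.
- *That the change score is biased by a known amount in a known direction.* The figures in step 2 need assumed D and r and a common mean. Step 3 reverses the conclusion under parallel change.
- *That adjusting for T0 cures the problem.* In step 4 the largest bias occurred after T0 adjustment. The Study 3 instruments include no measure of readiness to attend.
- *That all the covariates one would want are already in hand.* Measures lists six scales for Study 3. A sociodemographic section is described only for Study 1.

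**Conclusion.** The point holds for the comparison of attenders with the control group. That contrast rests on self-selection after baseline, plausibly related to the primary outcome, and the plan neither commits to handling it nor qualifies its causal wording. That attitude drives attendance is plausible but not documented.

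The size and direction of the bias are unknown. The -0.09 to -0.25 SD in step 2 is an illustration under stated assumptions, and the simulation shows that either sign is possible. The conclusion does not need a particular value: step 5 shows that a residual difference of 0.2 SD would already raise the false-positive rate from 5% to about 18%.

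**What to change.** 1. **Commit to adjustment.** For attenders v control, make covariate adjustment, or propensity or overlap weighting, mandatory and pre-specified. Use the T0 scales that Study 3 already lists (ATSPPH-S, GAD-7, PHQ-9, AUDIT, CAST, Fagerström), plus sociodemographic variables where they are recorded. Keep the unadjusted change-score contrast as a sensitivity analysis, because the two approaches rest on different assumptions.
2. **Show the imbalance.** Report a T0 balance table of attenders v never-attenders.
3. **Change the claim.** Replace the wording on effects attributable to the intervention by *association with attendance, adjusted for T0 characteristics*, and state that residual confounding by unmeasured motivation remains.

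**Cost.** For the six scales this is a change of text and analysis, best settled before the 9-month outcomes are analysed. Whether age, sex, migratory background and residence are recorded in Study 3 must be confirmed. If they are not, adding them would change data collection in a study that has been recruiting since January 2025 (Trial status). The scientific price is a weaker causal claim, and adjustment may still leave bias.

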**Fig. 1 Fig1:**
[figure not shown]
Procedure flowchart for longitudinal study (study 3)

### Measures

#### Study 1

The questionnaire will consist of two sections: one addressing sociodemographic questions and another utilizing standardized scales. The scales included are as follows:

**Food Insecurity Experience Scale (FIES)** [30–32]: An 8-item measure assessing the severity of food insecurity experienced, based on difficulties accessing adequate food.

**Childhood Trauma Questionnaire Short Form (CTQ-SF)** [33, 34]: A 28-item instrument evaluating various types of childhood trauma, including emotional, physical, sexual, and psychological trauma. An additional item has been included in this scale.

**Hopkins Symptom Check List 25 (HSCL 25)** [35–37]: A 25-item symptom inventory measuring anxiety (10 items) and depression (15 items).

**Barriers to Access to Care Evaluation (BACE-3)** [38, 39]: A 30-item tool assessing barriers to accessing mental health care, including stigma-related obstacles.

**Nightmare Severity Index (NSI)** [40]: A 9-item scale evaluating the nature of insomnia, satisfaction with sleep, and the impact of sleep disturbances on daily life.

**Alcohol Use Disorders Identification Test (AUDIT)** [41, 42]: A 10-item questionnaire designed to identify individuals at risk of alcohol addiction, addressing alcohol consumption, dependence, and related problems.

**Fagerström Test for Nicotine Dependence** [43, 44]: A 6-item questionnaire assessing the level of nicotine dependence in smokers.

**Cannabis Abuse Screening Test (CAST)** [45]: A 6-item screening tool to identify problematic cannabis use, particularly among adolescents and young adults, focusing on consumption habits and related issues over the past 12 months.

**Geometric Categorization Task (GeoCAT)** [46, 47]: A 6-item tool measuring primary and secondary cognitive processes.

#### Study 2

A semi-structured interview guide was developed based on a review of existing literature and preliminary interviews. The questions focus on participants’ life narratives and their experiences with substance use. The administration of the Rorschach test and the Adult Attachment Interview (AAI) will also be conducted. The Rorschach test is a “projective” psychological assessment composed of 10 cards depicting black-and-white and color inkblots. It allows for the assessment of an individual’s psychological functioning concerning certain fundamental competencies expressed through their engagement with the test material, such as their perception style, emotional expression, approach to interpersonal relationships, and significant individual characteristics and issues that reflect a singular mode of psychological organization [48]. The Adult Attachment Interview (AAI) is a 20-question interview designed to assess an individual’s attachment representations based on their recollections of early caregiving experiences. The responses are transcribed and analyzed using a rigorous coding system, classifying individuals into attachment categories such as secure, dismissing, preoccupied, or unresolved regarding trauma or loss [49, 50].

#### Study 3

**Generalized Anxiety Disorder (GAD-7)** [51–53]: A 7-item self-report questionnaire designed to assess the patient’s anxiety levels over the previous two weeks.

**Patient Health Questionnaire-9 (PHQ-9)** [54, 55]: A 9-item tool used for depression screening that also provides an indication of the severity of depressive symptoms.

**Alcohol Use Disorders Identification Test (AUDIT)** [41, 42]: A 10-item questionnaire designed to determine whether an individual is at risk of alcohol addiction. The items assess alcohol consumption, dependency, and related problems.

**Fagerström Test for Nicotine Dependence** [43, 44]: A 6-item questionnaire created to evaluate the level of nicotine dependence among smokers.

**Cannabis Abuse Screening Test (CAST)** [45]: A screening tool designed to identify problematic cannabis use, particularly among adolescents and young adults. It consists of six questions addressing consumption habits and associated problems over the past 12 months.

**Attitudes Toward Seeking Professional Psychological Help Short Form (ATSPPH-S)** [56, 57]: A 10- items psychometric scale designed to measure individuals’ attitudes toward seeking professional psychological help.

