## Methods/design

This research project is therefore structured around three complementary phases of study (Table 1), each based on a distinct methodological approach:

A **cross-sectional study (study 1)** that relies on a quantitative approach, conducted through the dissemination of online standardized questionnaires and scales (see: Measures) to young adults residing in partner structures at both regional and national levels. Its objective is to identify factors associated with addictive behaviors and to explore the links between trauma, migratory trajectories, food insecurity, psychological distress and perceived representations and barriers to accessing psychological care. These tools enable the rigorous collection of quantitative data and a multidimensional assessment to model the relationships between factors associated with the psychological and social challenges faced by this population. This study provides insights into general statistical trends.A **qualitative study (study 2)** adopting an exploratory perspective and aiming an in-depth understanding of the representations, subjective experiences, and individual and relational dynamics associated with addictive behaviors and trauma. The qualitative study builds upon the findings of Phase 1 by collecting clinical insights that provide a deeper understanding of the subjective dynamics of participants dealing with substance use issues and the obstacles encountered in their life trajectories that shape their relationship with care services.A **longitudinal study (study 3)** structured around a group intervention called the “Well-Being coffee group”, which operates as an open group (8 to 12 participants per session), conducted over six sessions, each lasting 1.5 to 2 h, held in the evening (6–8 PM) once a month for six months. Participation is voluntary for young residents in THP. The study aims to evaluate the impact of this group discussion format on participants’ psychological well-being, their perceptions of mental health, and their access to care.

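### Study 3 measures cannabis use with a 12-month recall at visits about 3 and 6 months after T0, so change in CAST is diluted toward no effect

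*Protocol article*

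**What the plan says.** Table 1 of the protocol article (Methods/design) gives the Study 3 main outcomes as "Substance use Perception of mental health care Wellness". Under Measures, Study 3, cannabis use is assessed with CAST: "It consists of six questions addressing consumption habits and associated problems over the past 12 months". The Study 1 entry for the same scale gives the same window ("focusing on consumption habits and related issues over the past 12 months"). No shortened version is mentioned.

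The group sessions run "once a month for six months" (Methods/design). The assessment points are "T0: prior to the program, T1: mid-program, T2: end of the program, T3: post-program follow-up". Procedures, Study 3, says the standardized questionnaires are completed at all four points. It does not list them scale by scale, and it does not except CAST.

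The only later time with a month attached is in Data analysis, Study 3: "The primary outcome measure is the variation in the total score on the ATSPPH-S at 9 months". The origin of those nine months is not given. The same section plans pre/post comparisons, dose-response analyses and linear mixed models over time.

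**The concern.** An outcome meant to show change over a programme of six months is measured by asking about the previous twelve. At a mid-programme or end-of-programme visit, the respondent is still reporting partly on the period before the programme began. A participant who cut down when the sessions started would report, at T1, on a year that was mostly spent at the old level.

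What is at stake is the substance-use question in Study 3. A real reduction in cannabis use would appear smaller than it is, and a small or null CAST result could then be reported as evidence that the groups do not influence use. No later analysis can undo this, because a 12-month answer does not contain recent use as a separate quantity.

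**Working it through.** The plan gives no figure of its own on this point, so the check is a direct calculation of the overlap.

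**Inputs**
- Recall window L = 12 months (Measures, Study 3).
- Programme length 6 months (Methods/design). Hence T1, mid-programme, is at about month 3, and T2, end of programme, at about month 6.
- T3 is not dated. The nine months given for the ATSPPH-S are taken first as counted from T0 (month 9), then as counted from programme end (6 + 9 = month 15).
- Assumptions: the programme starts at T0, and CAST is given at all four points.

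**Overlap**

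Pre-T0 months in the window at month t = max(0, 12 − t); share = that ÷ 12.

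| Visit | Month t | Pre-T0 months | Pre-T0 share | Post-T0 share |
|---|---|---|---|---|
| T1 | 3 | 12 − 3 = 9 | 75% | 25% |
| T2 | 6 | 12 − 6 = 6 | 50% | 50% |
| T3, nine months from T0 | 9 | 12 − 9 = 3 | 25% | 75% |
| T3, nine months from programme end | 15 | 0 | 0% | 100% |

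Assessments three months apart share 12 − 3 = 9 of their 12 months, so successive scores are also strongly linked by construction of the window.

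**What this does to a change in use**

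The overlap needs no model; translating it into attenuation does. Suppose the score reflects average use over the window.
- A full and lasting change at T0 would show as 3/12 = 25% of its size at T1, 6/12 = 50% at T2 and 9/12 = 75% at a month-9 T3.
- A change that began only at programme end would show as 0% at T2 and (9 − 6)/12 = 25% at a month-9 T3.

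**Illustration of scale**

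Participants, Study 3, assumes d = 0.7 with 55 per group at a significance level of 0.05. The power is not stated. A two-sided two-sample t-test with those values has 95% power. Under the averaging model with an unchanged SD:
- T1: 0.7 × 0.25 = 0.175, power 15%
- T2: 0.7 × 0.50 = 0.35, power 44%
- T3 at month 9: 0.7 × 0.75 = 0.525, power 78%

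These powers are before the planned Bonferroni correction. The d of 0.7 is the general planning value for Study 3 and is not tied to CAST, so these figures show scale only and do not predict the trial's result.

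**Control group**

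The controls answer with the same window. Each arm's post-T0 change is diluted by the same factor, so the difference between arms shrinks by that factor too.

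**After the fix**

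With a recall of about three months, the pre-T0 share is max(0, 3 − t) ÷ 3 = 0% at T1, T2 and T3.

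**The case against.** The strongest objection is that repeated use of CAST is inferred. Procedures, Study 3, says "Participants will complete standardized evaluation questionnaires at multiple time points (T0, T1, T2, T3") without naming scales. The sentence there on regular assessment of impact names anxiety, depression, attitudes and willingness to seek help, but not substance use. The Study 3 aim and the effects expected in the Discussion do not name it either, and the flowchart is not shown. This stands as a caveat. It does not remove the point, because Table 1 lists substance use as a main outcome, CAST is in the Study 3 battery, and nothing exempts it from the common schedule.

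Second, T3 is undated. This also stands. A reader might infer that every follow-up is contaminated; the documents support that only if T3 falls less than 12 months after T0. Nine months from T0 is the more natural reading, but it is not stated. T1 and T2 do not depend on it.

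Third, a reader might infer that a change in cannabis use would be invisible, or that a null result is built in. That goes too far: under the averaging model, up to 75% of an immediate change shows at month 9, and respondents may weight recent months more heavily. Nor is it true that answers about any use in the window cannot move before month 12. Someone whose last use was eight months before T0 is 8 + 6 = 14 months from it at T2 and drops out of the window, and a new user enters at once. The article does not give the response format of the items.

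Fourth, CAST is one of three substance-use scales in Study 3, the primary outcome is the ATSPPH-S, and the dilution cannot create a false benefit from a sustained change. All true, and it limits the weight of the point.

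**Conclusion.** The point holds for the cannabis part of the substance-use outcome in Study 3. If CAST is administered on the common schedule, about 75% of its recall window pre-dates T0 at T1 and about 50% at T2. At T3 the share is about 25% if T3 is nine months after T0, and nil if the nine months run from programme end. A sustained change in use is diluted toward no effect, both within groups and in the comparison with controls.

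The overlap shares rest on the stated window and programme length, on the programme starting at T0, and on the T3 reading given. The size of the attenuation rests further on how respondents weight the twelve months, which the documents do not settle. The primary analysis of the ATSPPH-S is untouched. The matter is worth correcting, but it does not threaten the main conclusion of Study 3.

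**What to change.** Keep the 12-month CAST at T0, as a measure of severity and for comparison with Study 1. For the change analysis, collect the cannabis items at T0, T1, T2 and T3 with one recall period no longer than the interval between assessments (about three months on the schedule inferred here), and analyse them as a continuous score. State which scales are given at which visit, and give the month of T3 counted from T0.

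The costs are a second set of six items at T0 and an altered instrument to which the standard cut-offs no longer apply. Participants enrolled before the change will have no short-window T0 value, and recruitment has been open since January 2025. Ethics committee approval may be needed, since Trial status requires it in advance for any substantial modification.

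If this is not feasible, add a statement at no cost: CAST change at assessments less than 12 months after T0 is attenuated by the recall window, and a null result will not be interpreted as absence of an intervention effect on cannabis use.
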